### Outcome Measures

#### Primary Outcome Measure

Cognitive assessment: CogTrack® is an online cognitive test battery consisting of 10 subtests, which, based on factor analysis, are combined into the following domains: attention, memory, and cognitive speed. There are 14 different word lists, each with 15 words, for the verbal memory test. The instructions are presented visually at the start of each testing session and also at the start of each task. In-task responses are made using the right arrow on the keyboard in two tasks and the left and right arrows in the other two. The participants are instructed to rest their finger(s) lightly upon the key(s) throughout each task. The speed and accuracy of every response are recorded. The primary outcome measure will be the quality of episodic memory combination of two accuracy scores from each of immediate and delayed word recall, word and picture recognition (four tasks in total), which has been shown to represent the overall quality of episodic memory and to be sensitive to cognitive changes, with negligible learning effects (39, 40). The battery is completed online monthly at home, using different word-lists at each occasion.

#### Secondary Outcome Measures

See test detail outlines in (39).

Secondary endpoints from the CogTrack System will include:
attentional intensity indexsustained attention indexcognitive reaction timeattentional fluctuation indexquality of working memoryspeed of memory retrieval.

### Safety and Handling of Adverse Events

Anthocyanins are safe (30), and there are no serious adverse effects to be expected. The study will nevertheless focus on safety, as explained later.

#### Recording Adverse Events

At each study visit, the participants are proactively asked about the occurrence of any adverse experiences, particularly about any abnormal bleeding since his/her last visit. The site SRA and SP will also assess adverse events by assessment of clinical and laboratory features. All adverse events, whether observed by the SP or elicited from or volunteered by the participant, will be documented. Blood is analyzed for safety with routine clinical analyses (liver, kidney, hematology, and international normalized ratio) at weeks 12 and 24. The electrocardiogram is taken at study inclusion and at week 24. Telephone and e-mail addresses of the SRA and SP are available to facilitate easy communication about possible adverse events. If dementia or other new medical conditions are detected during the screening process, this information is forwarded to the general practitioner if the participant agrees. If deemed necessary, action may also be taken by the SP.

#### Serious Adverse Events

Any serious adverse events during the study are recorded, and actions from the SRA and SP are taken as needed. The chief investigator (CI) is to be notified within 24 h of investigator awareness of the event.

### Emergency Unblinding

Given the safety profile of anthocyanins that have been reported (30, 43), we expect the need for emergency unblinding to be extremely rare. Nevertheless, we have the following procedure in case emergency unblinding is required:

If unblinding is deemed to be necessary for the event of significant concerns regarding participant safety, the CI will be notified immediately by the SP. If the CI considers emergency unblinding necessary, a request will be directed to appointed personnel at the MedPalett. The requested information will be transmitted to the requesting party. The CI will coordinate the process.

The actual allocation must not be disclosed to the participant or other trial personnel since the trial is placebo controlled-double-blind. Emergency unblinding should not necessarily be a reason for trial drug discontinuation. Details of any emergency unblinding shall be well-documented.

### Governance and Monitoring

The sponsor of the study is SUS. The clinical research group includes Ph.D. candidates, postdocs, and clinicians from the three different centers. A trial manager is in day-to-day charge of the trial and responsible for trial documentation, supporting the centers to recruit promptly, monitoring compliance with the protocol, and organizing meetings of the trial management group. This group includes CI, the local principal investigators, an external expert, and the trial manager. A decision-making group, with members from the clinical research group, will discuss relevant medical or ethical issues via e-mail.

### Data Storage

All parties will ensure the protection of subject personal data, and subject names or other identifiable data are not included in any reports, publications, or other disclosures, except where required by law. Data are stored securely, both on paper, on password-protected computers at the site, and encrypted online, at SUS with locked doors and shelves, with access only to dedicated study personnel.

### Statistical Considerations

#### Sample Size Calculations

The sample size calculations are based on published data on CogTrack (40). We will assume a Cohen's d effect size of 0.4, two-tailed testing at *p* < 0.05, at 80% power, which is considered to be a clinically relevant effect. A sample size of 110 patients per arm is required, allowing for ~10% dropout. Analyses will be adjusted for baseline scores for each test. *A priori* subgroup analyses are planned, including separate analyses of those with MCI vs. normal cognition, old vs. middle-aged (defined as above or below median age), participants with and without CMD, and those with normal and those with abnormal CSF AD markers, although the study is not powered for these analyses.

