Our main objectives for collecting neuroimaging and biological samples are to test whether relevant changes associated with dietary anthocyanin intake in participants with increased risk of progressive cognitive decline can be detected, for example, effects on the rate of loss of brain structure, cortical metabolic activity, and on oxidative and inflammation markers in the blood, CSF, and the microbiome.

Second, we will investigate whether any biomarker changes are associated with the various cognitive domains assessed with the cognitive tests.

We will also perform subgroup analyses to explore whether people with a CSF and/or MRI pattern typical of AD or cerebrovascular disease respond differently to anthocyanins compared with those without such changes. These biomarker analyses will be tentative, as the study is not powered for subgroup analyses but may be informative for planning a potential phase III trial.

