#### Randomization, Allocation and Blinding

Participants are randomized to anthocyanins or placebo in a 1:1 ratio based on stratified block randomization. The strata are made up of the combination of three treatment sites [Stavanger University Hospital [SUS], Akershus University Hospital [Ahus], Oslo, and Betanien Hospital, Bergen] and two recruitment groups, that is, those who are recruited due to CMD criteria only vs. those who are recruited due to cognitive criteria with or without CMD criteria. Within each of the six strata, the randomization is performed in blocks of varying sizes (four or six) to ensure local balance and non-predictability of allocation. The randomization lists with ID numbers and anonymous treatment arms (“A” and “B”) are produced by the study statistician and sent to the production site, which is instructed to do a random allocation (using a dice) to specify which of A and B should be the intervention arm. The capsules (anthocyanins and placebo) are produced according to the randomization lists, marked with ID numbers, and distributed to the participating centers. At the centers, the participants are numbered consecutively at their inclusion in the study. All study staff, participants, and the data analyst remain blinded to the actual treatment given until data have been analyzed.

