## Discussion

Out of 236 participants who have been assessed for eligibility, 50 participants were excluded (49 not meeting the inclusion criteria, and one declined to participate). As of the end of February 2020, 181 participants have been randomized; 123 in the CMD group and 58 in the MCI group. Among the strengths of this trial is the relatively large sample size, making it one of the largest anthocyanin trials and sufficiently powered to detect a medium effect of anthocyanins on primary cognitive outcome measures. The use of web-based cognitive assessment enables frequent testing without learning effects, which is increasing the statistical power. The comprehensive acquisition of biomarkers allows for a detailed mechanistic study of anthocyanin effects. Finally, the collection of blood and CSF for anthocyanin metabolite analyses allows for analysis of dose effects. However, some limitations of this trial are the lack of dietary records and not giving specific dietary instructions concerning the intake of anthocyanin-rich foods. However, participants are asked to maintain their habitual diet during the intervention period. Of note, applying any dietary restrictions in a long-term trial lasting 24 weeks might challenge participant's compliance. Importantly, the study has a washout period of 12 months after any Medox® intake to provide a period of abstinence from the interventional product.

The 6 months' trial duration is similar to previous trials with cholinesterase inhibitors and expected to be sufficiently long to detect differences in terms of symptoms but might be too short to detect disease-modifying effects on the risk to progress to dementia or biology. The number of participants with MCI is lower than the group with CMD, resulting in reduced power for sub-analysis in this group. The participants are largely ethnic Norwegian, that is, Caucasians, with relatively high socioeconomic status and educational level. Thus, the findings might not be immediately relevant to other populations. Some initial characteristics based on the first 86 randomized participants at SUS (pre-intervention) are displayed in Table 3. Finally, anthocyanins might have biological effects, for example, stool color change or constipation, with the risk for participants or research staff to become unblinded. However, there might be many possible explanations for any such changes unrelated to the study.

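### The stated question about different response by CSF/MRI pattern calls for an interaction estimate, but the subgroup plan specifies separate within-group analyses, which do not estimate a difference in effect

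*Protocol article*

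**What the plan says.** Three places in the protocol article bear on this.

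- **Screening Procedures** (under Trial Procedures and Rationale) poses the question: do people with a CSF and/or MRI pattern typical of Alzheimer's or cerebrovascular disease "respond differently to anthocyanins compared with those without such changes"? It calls these biomarker analyses tentative and says they may help plan a possible phase III trial.
- **Sample Size Calculations** gives the method. The a priori subgroup analyses include "separate analyses of those with MCI vs. normal cognition, old vs. middle-aged (defined as above or below median age" and go on to "participants with and without CMD, and those with normal and those with abnormal CSF AD markers, although the study is not powered for these analyses".
- **Discussion** adds: "The number of participants with MCI is lower than the group with CMD, resulting in reduced power for sub-analysis in this group".

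Planned Statistical Analyses describes the primary analysis, a mixed model for repeated measures with the week-24 contrast between arms. It defers detail to an analysis plan to be finalised before unblinding. The article nowhere names a treatment-by-subgroup interaction or any other between-subgroup contrast.

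**The concern.** Whether two groups respond differently is a question about the difference between two treatment effects, that is, an interaction. Separate analyses answer another question: is there evidence of an effect within this group? If one group reaches significance and the other does not, that does not show that the effects differ, least of all when the groups differ in size and neither comparison is well powered.

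The mismatch is explicit for the CSF Alzheimer-marker split, which serves the question written under Screening Procedures. For MCI, age and cardiometabolic disorder the interest in a difference is implied by the paired layout of the subgroups but is not written out.

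At stake is the reading of the secondary results. If the effect were the same in everyone, the separate tests would still often suggest that it is confined to one group, more often the larger one. Such a pattern could then colour the choice of population for a later trial.

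**Working it through.** **Inputs from the article**

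- Effect size and test: d = 0.4, two-sided alpha 0.05, power 80% (Sample Size Calculations).
- Size: "A sample size of 110 patients per arm is required, allowing for ~10% dropout" (same section).
- Allocation: "Participants are randomized to anthocyanins or placebo in a 1:1 ratio based on stratified block randomization" (Randomization, Allocation and Blinding).
- Mix at the end of February 2020: 58 of 181 randomised were in the MCI group and 123 in the cardiometabolic group (Discussion).

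**The plan's own figure.** n per arm = 2(1.960 + 0.842)²/0.4² = 98.1, rounded up to 99. Then 99/0.9 = 110, which matches. With 99 evaluable per arm, the total is 198.

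**Subgroup sizes, MCI split** (mix carried to 220, 10% dropout in both groups)

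- MCI: 58/181 × 220 = 70.5; × 0.9/2 = 31.7 per arm.
- Non-MCI: 123/181 × 220 = 149.5; × 0.9/2 = 67.3 per arm.

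**Power of each separate test** when the true effect is d = 0.4 in both groups: a two-sample t-test gives 0.348 (MCI) and 0.634 (non-MCI). The normal approximation gives 0.357 and 0.641.

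**Chance that exactly one test is significant**, p₁(1 − p₂) + p₂(1 − p₁):

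- only MCI: 0.348 × 0.366 = 0.127
- only non-MCI: 0.634 × 0.652 = 0.413
- total: about 0.54

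The normal approximation also gives 0.54 (0.128 + 0.412), and a simulation of 400,000 trials gave 0.541. Among simulated trials with a significant overall result, the two tests disagreed in 62%.

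**Interaction instead.** SE = √(2/31.7 + 2/67.3) = 0.305 SD, so the 95% CI half-width is 1.96 × 0.305 = 0.60 SD. With a common effect, the simulated false-positive rate was 4.9%. Power to detect a between-group difference of 0.4 SD is only 26%, and the difference detectable with 80% power is (1.960 + 0.842) × 0.305 = 0.85 SD.

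**Other splits** (normal approximation, same 198 evaluable)

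| Split | Per arm | Power | Exactly one significant |
|---|---|---|---|
| Median age | 49.5 / 49.5 | 51% / 51% | 50% |
| CSF markers, if 20% in the smaller group | 19.8 / 79.2 | 24% / 71% | 61% |
| CSF markers, if 10% in the smaller group | 9.9 / 89.1 | 14% / 76% | 69% |

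The article gives no CSF split. The 10% and 20% rows are assumptions, and they also assume a CSF result for everyone.

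**If there is no effect at all**, exactly one of two tests is significant in 2 × 0.05 × 0.95 = 9.5% of trials.

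**The case against.** The strongest reply has four parts.

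- **The question is narrower than the method.** A difference in response is asked about only for CSF and MRI patterns. Describing the effect within people with MCI, or within an age group, is a legitimate aim of its own. This stands: a reader might infer that the article states a differential-response objective for every subgroup, and it does not. The direct mismatch is with the CSF-marker split. The same reasoning reaches MCI, age and cardiometabolic disorder only by implication.
- **The analysis plan may supply the interaction.** The list of subgroup analyses is worded as non-exhaustive, and details are deferred. This also stands as far as it goes: one cannot conclude that no interaction will be tested. But the article does more than leave the method open. It names one, and that method does not fit the question.
- **The article already warns the reader.** It says the study lacks power for subgroups, calls the biomarker analyses tentative, and notes the reduced power in MCI. Nowhere does it say that p-values will be compared across subgroups. The warnings lower the risk of a bad conclusion but do not repair the method, because low and unequal power is what makes the separate tests disagree.
- **The 54% is not the rate of one error.** It counts both directions and presumes d = 0.4 in everyone. This is correct. The pattern in which only the larger group seems to respond occurs in about 41%.

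The median cut for age might also be read as an error, since it does not say where a participant exactly at the median belongs. That is a matter of wording, and a prespecified median split is inefficient rather than wrong.

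**Conclusion.** The point holds in limited form. The article asks whether groups defined by CSF/MRI pattern respond differently, and the analysis it specifies for the related subgroups does not estimate that difference. With a common effect of d = 0.4, the two separate MCI-split tests would disagree in about 54% of trials (41% only non-MCI, 13% only MCI), against 5% false signals from an interaction test.

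These figures rest on five assumptions: the February 2020 mix carries to 220; dropout is 10% in both groups; the SDs are equal; the MCI recruitment group stands for the MCI subgroup; and the week-24 contrast is approximated by a two-sample comparison. With no true effect, disagreement falls to 9.5%.

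A reader might infer that the trial's main result is at risk, or that a later trial will be sent to the wrong population. The documents support neither. The primary analysis and the sample size are unaffected, and the article offers the biomarker subgroup results only as tentative input to planning. The change should still be made, because it is easy to fix before unblinding.

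**What to change.** For each pre-planned subgroup factor, replace the separate analyses with the primary mixed model fitted to all participants (for CSF markers, all with a result). Add the subgroup, subgroup-by-visit, treatment-by-subgroup and treatment-by-subgroup-by-visit terms. Then:

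- report the week-24 interaction estimate with its 95% CI;
- show subgroup effects from that same model, with intervals, as description only;
- state that no differential effect will be claimed from within-subgroup p-values.

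Entering age as a continuous modifier is an optional refinement.

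The cost is a few sentences in the analysis plan and slightly longer model code, with no extra participants or data. The downside is imprecision: for the MCI split the standard error is about 0.30 SD, so the interval will usually be too wide to establish or exclude a moderate difference. That imprecision is the uncertainty readers should see.

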#### Planned Statistical Analyses

The primary analysis will be the comparison between the active and placebo groups on CogTrack quality of memory domain score change during follow-up. The primary study population will be a modified intention-to-treat population, that is, all participants having ingested at least one capsule and with at least one follow-up assessment.

Summary statistics (n, mean, standard deviation, and minimum and maximum scores) will be calculated by treatment arm for the data at each testing session, and, additionally, for the change from baseline scores. A mixed model for repeated measures ANCOVA will analyze the change from baseline scores. The primary comparison will be the contrast (difference in least-square means) between active and placebo at the end of the study (week 24) (44). A detailed statistical analysis plan will be finalized before the unblinding of data.

#### Trial Status

The study started the recruitment of participants in April 2018. We are expecting to reach the recruitment target in summer 2020 and expect completion of the study during 2020.

## Discussion

Out of 236 participants who have been assessed for eligibility, 50 participants were excluded (49 not meeting the inclusion criteria, and one declined to participate). As of the end of February 2020, 181 participants have been randomized; 123 in the CMD group and 58 in the MCI group. Among the strengths of this trial is the relatively large sample size, making it one of the largest anthocyanin trials and sufficiently powered to detect a medium effect of anthocyanins on primary cognitive outcome measures. The use of web-based cognitive assessment enables frequent testing without learning effects, which is increasing the statistical power. The comprehensive acquisition of biomarkers allows for a detailed mechanistic study of anthocyanin effects. Finally, the collection of blood and CSF for anthocyanin metabolite analyses allows for analysis of dose effects. However, some limitations of this trial are the lack of dietary records and not giving specific dietary instructions concerning the intake of anthocyanin-rich foods. However, participants are asked to maintain their habitual diet during the intervention period. Of note, applying any dietary restrictions in a long-term trial lasting 24 weeks might challenge participant's compliance. Importantly, the study has a washout period of 12 months after any Medox® intake to provide a period of abstinence from the interventional product.

The 6 months' trial duration is similar to previous trials with cholinesterase inhibitors and expected to be sufficiently long to detect differences in terms of symptoms but might be too short to detect disease-modifying effects on the risk to progress to dementia or biology. The number of participants with MCI is lower than the group with CMD, resulting in reduced power for sub-analysis in this group. The participants are largely ethnic Norwegian, that is, Caucasians, with relatively high socioeconomic status and educational level. Thus, the findings might not be immediately relevant to other populations. Some initial characteristics based on the first 86 randomized participants at SUS (pre-intervention) are displayed in Table 3. Finally, anthocyanins might have biological effects, for example, stool color change or constipation, with the risk for participants or research staff to become unblinded. However, there might be many possible explanations for any such changes unrelated to the study.

**Table 3 T3:** Some initial baseline characteristics based on the first 86 randomized participants at SUS.

**Variables**	**Both groups (*n* = 86)**	**CMD group (*n* = 60)**	**MCI group (*n* = 26)**
Men, n (%)	47 (55%)	33 (55%)	14 (54%)
Age in years	68 (65, 74)	68 (64, 74)	69 (66, 76)
Education in years	14 (11, 16)	14 (11, 16)	14 (12, 17)
MMSE score	29 (28, 30)	30 (28, 30)	29 (27, 30)
No. of concomitant medications	3 (2, 5)	3 (2, 5)	2 (1, 4)

*Data are presented as median (interquartile range, IQR) unless otherwise specified*.

*SUS, Stavanger University Hospital; CMD, Cardiometabolic disorders; MCI, mild cognitive impairment; MMSE, Mini-Mental Status Examination*.

## Ethics Statement

The studies involving human participants were reviewed and approved by The Norwegian regional ethics committee (2017/374). The patients/participants provided their written informed consent to participate in this study. The trial has been registered at: http://www.clinicaltrials.gov/, NCT03419039.

## Service User Involvement

The valuable feedback provided by our participants in our pilot study (30) was taken into consideration in developing the anthocyanins in people at risk for dementia study design. The user involvement representatives at the center for age-related medicine at SUS have contributed by giving their inputs and recommendations to develop the advertising flyers and have also helped to promote the publicity of the study and recruitment. Also, there is a plan for user involvement also in interpretation, dissemination, and presentation of the study outcome.

